**Results:**

This study aimed to determine whether TNRM-UN is more effective than current acupuncture therapies by providing compelling evidence and deciding whether TNRM-UN can be used as a promising therapy for CV with a deficiency of qi and blood.

**Clinical trial registration:**

https://www.chictr.org.cn/, identifier: ChiCTR2400080759.

## Introduction

Cervical vertigo (CV) is a broad term encompassing dizziness caused by various cervical pathologies. In contrast, cervical spondylosis-induced vertigo refers to dizziness resulting from degenerative changes in the cervical spine, such as osteophyte formation or intervertebral disc herniation. This study focuses on the latter, as defined by the inclusion criteria. CV is associated with various symptoms such as disequilibrium, light-headedness, tinnitus, nausea, migraine, and neck pain or stiffness (1, 2). It has been reported that the estimated prevalence of CV is between 3.8% and 17.6%. Approximately 50% of patients with cervical spondylosis have vertigo symptoms (3), while 65%−66% of vertigo in elderly patients is attributed to cervical spine dysfunction (4). TCM considers that middle-aged and elderly people suffer from CV mostly due to insufficient kidney essence and deficient qi blood biochemistry. Therefore, this study is specifically concerned with CV related to qi and blood deficiency. In recent years, with the widespread use of electronic devices, the onset of CV issues has occurred at a younger age, and the risk of developing stroke and syncope is higher (5). Therefore, major academic circles are paying more attention to this disease, and it is particularly important to explore its pathogenesis, diagnostic ideas, and more effective treatment methods.

So far, modern medicine has believed that the pathological mechanism of CV primarily involves the following theories: (1) Abnormal proprioceptor theory (6). (2) sympathetic nerve theory (7), (3) vertebral artery theory (8), (4) migraine-related theory (9), and (5) neurohumoral factor theory (10). In addition, with the progression of the disease, patients will gradually develop psychiatric factors such as anxiety and depression, which may reduce the patients' self-regulatory function and make the clinical efficacy unsatisfactory (11). Multiple mechanisms, with a dominant mechanism, usually act together in CV. Currently, to address these pathological mechanisms, the main treatment options for CV include drug and surgical therapy in modern medicine. Drug treatment primarily aims to enhance microcirculation, eliminate aseptic inflammatory reactions, and alleviate muscle tension (12). Surgical treatment is mainly to relieve sympathetic nerve stimulation, eliminate mechanical compression of the vertebral artery, and rebuild the stability of the cervical spondylosis segment (13). However, drug treatment has high recurrence and certain toxic side effects, while surgical treatment has the disadvantages of high risk, high cost, and immature surgical techniques, which affect the efficacy (14).

The TCM categorizes CV as “cervical paralysis” and “vertigo.” TCM believes that the pathogenesis of CV is mainly due to a deficiency of qi, blood, and the brain medulla. These mechanisms are similar to the theory proposed by modern medicine that CV is caused by an insufficient blood supply to the vertebral arteries. In addition, patients with CV are often accompanied by emotional problems such as restlessness of the heart and mind and depression of liver qi, which makes it difficult to cure the disease. In recent years, TCM has achieved satisfactory results in treating CV. TCM therapies mainly involve Chinese herbal medicine, manual repositioning, acupuncture, massage, cervical traction, and needle-knife therapy (15–20). However, the experimental designs of most clinical trials were not rigorous enough, and it was insufficient for evidence-based medical thinking. These TCM methods (15–20) only have only shown their effectiveness for this disease, and there were shortcomings such as longer treatment course, slower apparent effect, and higher recurrence rate in clinical practice. The author has done a systematic review and meta-analysis (21) that has supported the efficacy of acupuncture for CV. The author has followed [name] cervical vertigo treatment team in clinical practice and experimental research for decades has found that treating CV with qi and blood deficiency is closely related to the regulation of the governor vessel and conception vessel. In recent years, the author has successively established “Dredging governor vessel therapy (22)” and “Dredging governor-regulating conception vessel acupuncture method (23)” to treat CV with deficiency of qi and blood. However, there were still the following shortcomings: (1) Acupuncture therapies brought more pain to patients because of puncturing more acupoints, (2) these therapies did not consider emotional factors, and (3) there were no relevant statistics to long-term efficacy.

To avoid these shortcomings, the efficacy, safety, and cost-effectiveness of TNRM-UN will be compared to those of TNRM-TA or UN through a rigorously designed randomized controlled trial, which will provide a clinical basis for using TNRM-UN for CV with a deficiency of qi and blood.

## Methods and design

This is a single-center, assessor- and analyst-blinded randomized controlled trial including three parallel groups, which are TNRM-UN, TNRM-TA, and UN groups. The trial will follow the guidelines of the Standards for Reporting Interventions in Clinical Trials of Acupuncture (STRICTA) (24) and the Standard Protocol Items: Recommendations for Interventional Trials (SPIRIT) (25). This study will include 6 weeks of treatment and 24 weeks of follow-up. The study period was July 2023 to December 2025. Figure 1 presents a flowchart of the trial, and Table 1 shows all schedules.

**Figure 1 F1:**
[figure not shown]
Flowchart of this study.

**Table 1 T1:** Schedules of this study.

	**Baseline**	**Treatment (weeks)**	**Follow-up (weeks)**	
**Time point**	**Week 0**	**Week 6**	**Week 12**	**Week 24**
**Enrolment**				
Eligibility screening	O			
Informed consent	O			
Allocation	O			
**Intervention**				
TNRM-UN		O		
TNRM-TA		O		
UN		O		
**Outcome assessments**				
(1) CVS-FAS	O	O	O	O
(2) QBD-SAS	O	O	O	O
(3) VA-DV	O	O		
(4) VA-PSV	O	O		
(5) VA-EDV	O	O		
(6) VA-PI	O	O		
(7) VA-RI	O	O		
Safety evaluation		O	O	O

O, required; TNRM-UN, three-needle of regulating the mind combined with umbilical needle; TNRM-TA, three-needle of regulating the mind combined with traditional acupuncture; UN, umbilical needle; CVS-FAS, Cervical Vertigo Symptom and Functional Assessment Scale; QBD-SAS, qi and Blood Deficiency Symptoms Assessment Scale; VA-DV, vertebral artery diameter value; VA-PSV, vertebral artery peak systolic velocity; VA-EDV, vertebral artery end diastolic velocity; VA-PI, vertebral artery pulsatility index; VA-RI, vertebral artery resistance index.

### Participant recruitment

Participants will be mainly recruited from the Third People's Hospital of Xiaoshan District, Hangzhou. Outpatients or inpatients from the department of acupuncture and neurology will be recruited. Epidemiological data from our hospital indicated that approximately 60%−70% of CV patients present with deficiency of qi and blood syndrome, aligning with regional demographic trends (26). We have found that 85% of screened patients met the deficiency of qi and blood criteria through screening logs, which ensured sufficient representation. So, recruitment gives priority to CVs with a deficiency of qi and blood. Some news media platforms, including exhibition shelves, the hospital's official account, and relevant newspaper columns, will be used to supplement participant enrollment. These platforms will refer to brief introductions of this study and the researchers' contact information. The researchers will thoroughly document this trial course for every participant and request them to sign an informed consent form.

### Diagnosis criteria

#### Western medical diagnostic criteria

This refers to the diagnostic criteria formulated by the Third National Symposium on Cervical Spine Disease (2008) (27).

(1) Patients had a history of sudden collapse episodes with cervical vertigo.

(2) The neck rotation test was positive.

(3) Patients tend to have cranial symptoms, including blurred vision, tinnitus, and hearing disorders.

(4) Radiographs showing segmental instability or osteophytes of the hook vertebral joint.

(5) Magnetic resonance imaging (MRI) or vertebral artery ultrasonography revealed local stenosis or tortuosity of the second vertebral artery (V–II).

#### Chinese medicine diagnostic criteria

It refers to “TCM diagnostic efficacy criteria” formulated by the Department of Medical Affairs of the State Administration of Chinese Medicine (28).

(1) In mild cases, dizziness or vision rotation can be stopped by closing the eyes, but in severe cases, the patient may feel like riding in a car, boat, or even falling down.

(2) CV may be accompanied by nausea and vomiting, tinnitus, deafness, sweating, and pallor.

(3) CV has a chronic onset that progressively worsens, an acute onset, or recurrent attacks.

#### Classification criteria of qi and blood deficiency

It refers to the syndrome differentiation basis of qi and the blood deficiency type formulated by the internal Medicine of TCM (29).

(1) Vertigo occurred during exertion and was exacerbated during exercise.

(2) Pale complexion and lack of gloss.

(3) Heat palpitates, sleepless, tired, and lazy.

(4) Faint tongue and weak pulses.

### Inclusion criteria

(1) The diagnostic criteria for CV in Chinese and Western medicine and the classification standard for qi and blood deficiency.

(2) Age 20 ≤ age ≤ 75 years, regardless of sex.

(3) Participants could adhere to the therapy plan and did not concurrently participate in other clinical trials.

(4) The participants voluntarily signed informed consent forms.

### Exclusion criteria

(1) Participants diagnosed with other TCM types of CV.

(2) Participants diagnosed with vertigo of heart, brain, and ear origin.

(3) Participants with combined cardiac, cerebral, renal, and other serious primary illnesses.

(4) Participants with abnormal blood flow parameters in segments I and III of the vertebral.

### Discontinuation or elimination criteria

(1) Participants were mistakenly included in the trial.

(2) Participants experienced serious adverse events (AEs) and did not consistently participate in the study.

(3) Participants suffered serious complications during the course of the trial, which required emergency care.

(4) Participants with personal factors were asked to stop the trial.

(5) Participants with poor compliance did not adhere well to the study process.

(6) The participants received treatment outside the intervention.

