### Intervention

Each group will be divided into 33 participants who received TNRM-UN, TNRM-TA, and UN treatments separately for 6 weeks. The frequency of the intervention is 3 times per week, and the needles are left in place for 30 min.

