### Outcome measures

All outcome measurements will be assessed before treatment and after 6 weeks of treatment, and primary outcomes will also be assessed at 12, 24 weeks follow-up.

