### Safety evaluation

Acupuncture-associated adverse events (AEs) include intolerable pain, bleeding, local hematoma, and other uncomfortable feelings after acupuncture (e.g., pale face, cold, moist limbs, cold sweat, dizziness, nausea, rapid heartbeat, weak pulse, and even fainting). All AEs, which will be considered as unrelated, possibly related, or related to treatment, will be recorded and assessed by investigators on an adverse event. Investigators should record in detail the occurrence date, degree [mild, moderate, or severe (41)], duration of symptoms, and emergency measures of AEs.

Timely rescue measures will be taken for serious adverse events. Simultaneously, researchers will immediately report to the Ethics Committee, which will decide whether to withdraw the participants from the study.

To comprehensively assess delayed-onset AEs and acupuncture safety, we will take the following measures: (1) Extended follow-up duration: Participants will receive monthly telephone follow-ups for 6 months post-trial completion (up to week 48) to capture delayed-onset AEs. (2) Patient-reported outcome diaries: Participants will document daily symptoms (e.g., pain and numbness) in a standardized diary for 12 weeks post-treatment. (3) Electronic Health Record (EHR) Linkage: With participants' consent, we will access electronic health records for a 1-year post-trial to identify their hospitalizations or diagnoses potentially linked to acupuncture.

Standardized Criteria for AE Causality Assessment will adopt the following measures: (1) WHO-UMC Causality Criteria (42): (a) Certain: AE occurs post-treatment, aligns with known acupuncture effects, and resolves upon discontinuation. (b) Probable/likely: Temporal association with no confounding factors. (c) Possible: Plausible link, but alternative explanations exist. (d) Unlikely: No plausible connection to treatment. (2) Naranjo algorithm (43): A quantitative tool to score causality likelihood (scores: ≥5: “probable”; ≤ 1: “doubtful”). (3) Independent adjudication: A blinded Safety Review Board (SRB) comprising a neurologist, TCM expert, and pharmacovigilance specialist will resolve disputed cases.

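### The serious-harm items in the discontinuation or elimination criteria allow follow-up to end or data to be removed, including after needling has finished at week 6

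*Protocol article*

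**What the plan says.** All references are to the protocol article.

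- **Discontinuation or elimination criteria.** Item (2): "Participants experienced serious adverse events (AEs) and did not consistently participate in the study". Item (3): "Participants suffered serious complications during the course of the trial, which required emergency care". The section uses one heading for six items. It does not say which items lead to discontinuation and which to elimination, or whether treatment, study or analysis is meant. Item (3) covers the whole trial, not only the treatment phase.
- **Safety evaluation.** For serious adverse events, "researchers will immediately report to the Ethics Committee, which will decide whether to withdraw the participants from the study".
- **Intervention.** Needling has a fixed end: "Each group will be divided into 33 participants who received TNRM-UN, TNRM-TA, and UN treatments separately for 6 weeks".
- **Outcome measures and Table 1.** All outcomes are measured at baseline and week 6, and "primary outcomes will also be assessed at 12, 24 weeks follow-up". Table 1 also schedules safety evaluations at weeks 6, 12 and 24.
- **Other safety capture (Safety evaluation).** Adverse events are recorded with date, severity, duration and measures taken. In addition, "Participants will document daily symptoms (e.g., pain and numbness) in a standardized diary for 12 weeks post-treatment"; "Participants will receive monthly telephone follow-ups for 6 months post-trial completion (up to week 48) to capture delayed-onset AEs"; and, with consent, "we will access electronic health records for a 1-year post-trial to identify their hospitalizations".
- **Statistical analysis plan, item (4)(b).** Multiple imputation under missing-at-random is a sensitivity analysis. Its model may include adverse events that occur after dropout.

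**The concern.** Stopping an intervention after a serious event protects the participant. Stopping measurement, or removing what has been measured, does not. The two criteria and the Ethics Committee sentence do not draw that line, and the words they use (elimination; withdrawal from the study) reach beyond needling.

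This matters because items (2) and (3) select participants by harm. If follow-up ends or data are dropped for them, the missing scores are not a random subset. They may come from people who did badly, and more of them may be in one arm. Item (3) is not limited to complications caused by needling. The diagnostic criteria include a history of sudden collapse, so an emergency attendance during follow-up could be a relapse, which the week 12 and week 24 scores are there to show. That such an event would be counted under item (3) is an inference, but nothing in the text excludes it.

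An analysis plan can define who is analysed. It cannot recover a week 12 or week 24 score that was never taken. Whether visits continue after a harm event therefore has to be settled in the rules for trial conduct.

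**Working it through.** The plan gives no figure on this point, so there is none to reproduce. The check sets the rules against the schedule, then gives an illustrative size.

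**Step 1: how much of the trial lies after needling.** Inputs: 6 weeks of treatment (Intervention) and visits at weeks 0, 6, 12 and 24 (Table 1).
- By Table 1: (24 − 6)/24 = 18/24 = 75% of the trial.
- If the 24 weeks of follow-up start after treatment (one reading of Methods and design): 24/(6 + 24) = 24/30 = 80%.
- Either way, 2 of the 3 post-baseline visits for the primary scales come after the last needling session.

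**Step 2: what can be lost per participant.** Scores = 2 scales × remaining visits.

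| Time of event | Primary-scale scores | Safety evaluations | Ultrasound |
|---|---|---|---|
| Before week 6, only if read as leaving the study | up to 2 × 3 = 6 | up to 3 | week 6 |
| Weeks 6 to 12 | 2 × 2 = 4 | 2 | none |
| Weeks 12 to 24 | 2 × 1 = 2 | 1 | none |

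**Step 3: whether other provisions secure these items.**
- The triggering event is recorded and, if serious, reported to the Ethics Committee at once. It is not lost.
- Diaries, calls and record linkage gather safety information. None yields a CVS-FAS or QBD-SAS score.
- The calls are described as following trial completion, and the extension to 48 weeks (Limitations, item (5)) is for those who complete the trial. The text does not say whether a withdrawn participant would be included in either.
- Imputation can use a recorded adverse event as a predictor. It does not replace a score that could have been collected.

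**Step 4: illustrative shift in one arm's mean.** Inputs: 33 randomised per arm, pilot mean reduction 7.3, SD 8.2, δ = 5 (Sample size estimation). If one of 33 is removed from the analysis, the arm mean moves by gap/33, where gap = mean improvement of those kept minus improvement of the one removed. Those kept are taken to improve by 7.3.
- Removed participant unchanged: gap 7.3; 7.3/33 = 0.22 points.
- Removed participant worse by one SD: gap 7.3 + 8.2 = 15.5; 15.5/33 = 0.47 points.

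Both gaps are assumptions. The figures apply to a time point at which the participant is absent from the analysis. If only follow-up stops after week 6, the week 6 score already exists and the week 6 mean does not move.

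**The case against.** The case on the other side has several parts.

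- **The rule may do nothing after week 6.** A reader might infer that, once needling is over, item (3) can only end follow-up or delete data. The text does not force this. If discontinuation means stopping treatment, the item may simply have no effect after week 6, and no section says that collected scores are deleted. What stands is that the wording permits the other readings.
- **The rules conflict.** A reader might see a contradiction between the fixed criteria and the Ethics Committee's discretion. They can be read together: the criteria give grounds and the Committee decides. That also means withdrawal need not be automatic. But the Committee's stated question is withdrawal from the study, and nothing says that assessments continue when only needling should stop.
- **Harms data are lost.** This is too strong. The event itself is captured, and diaries, calls and record linkage add more. What is exposed is the later scores and up to three scheduled safety evaluations.
- **The bias is large.** One could assume that all 33 − 30 = 3 budgeted dropouts in an arm are such cases, giving 3 × 0.22 = 0.66 or 3 × 0.47 = 1.41 points. The documents do not support that. The 10% allowance is for dropout in general, and a shift in one arm becomes bias of that size in the comparison only if the other arm has no similar removals.
- **Events will be rare.** The Discussion cites one acupuncture study with 0.0% adverse reactions and another with no severe ones. These are not planning rates, and item (3) is not confined to acupuncture reactions, but a very small number is likely.
- **This is a condensed article.** Detail on follow-up after discontinuation may be in a full protocol. The point here, however, concerns rules that the article does state.

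**Conclusion.** The concern holds in a limited form. Items (2) and (3), together with the Ethics Committee sentence, permit follow-up to end or data to be removed for participants selected by harm, and item (3) does so throughout the trial, including the 75% to 80% of it when no needling remains. Two to four primary-scale scores and one or two safety evaluations are exposed per participant with an event after week 6, and more for an earlier event if the rule is read as leaving the study.

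The documents give no event rate, so the size of any bias is unknown. Per participant removed from the analysis, an arm's mean CVS-FAS change would move by about 0.2 to 0.5 points under the two assumed gaps, which is 0.22/5 = 4% to 0.47/5 = 9% of δ. These percentages are a yardstick only, because δ is a difference between arms. The reason to act is complete follow-up and freedom from outcome-related exclusion, not power. It is a cheap improvement rather than a threat to the trial.

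**What to change.** Reword items (2) and (3) and the Ethics Committee sentence in Safety evaluation, identically for all three arms, to state that:

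1. such an event stops any remaining study needling;
2. the remaining week 6, 12 and 24 CVS-FAS, QBD-SAS and safety evaluations continue, unless the participant withdraws consent or the Ethics Committee decides in that case that participation must end;
3. all data collected stay in the analysis of the randomised group.

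This leaves the case-by-case decision with the Ethics Committee and keeps the participant's right to withdraw. It needs a short wording amendment, an instruction to the site and a few retained visits. Sample size and outcomes do not change.

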### Randomization and allocation concealment

Participants will be randomly categorized into TNRM-UN, TNRM-TA, or UN groups; the details of the allocation are as follows:

Randomization sequence generation (30): A statistician independent of the research team will generate the randomization sequence using Statistical Package for the Social Sciences (SPSS) version 25.0 (IBM Corp, USA) with a block randomization method. Sequences will be stratified by baseline CVS-FAS score and age to ensure balance between groups. The randomization list is password-protected and stored on a secure server accessed only by an independent statistician.

Allocation concealment protocol (31): Group assignments are sealed in sequentially numbered, opaque envelopes. Each envelope contains a folded card with the group assignment (TNRM-UN, TNRM-TA, or UN). The coordinator, uninvolved in recruitment or outcome assessment, opens envelopes in sequential order only after confirming participant eligibility. Envelopes are stored in a locked cabinet, and an external auditor will access logs weekly.

Preventive Measure of Bias: Participants and outcome assessors are blinded to group assignments. Acupuncturists could not be blinded due to procedural differences, but are instructed not to discuss treatment details. The statistician analyzing outcomes will receive anonymized datasets labeled “Group A/B/C,” and group identities are revealed only after final analysis.

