### Blinding method

The participants will not be blinded due to the completely different therapies used in the three groups. Meanwhile, owing to the unique nature of acupuncture, it is unrealistic to turn a blind eye to acupuncture operators. However, manipulation, evaluation, and data analysis will be performed by independent Investigators. The evaluators and statisticians are blinded to the grouping information.

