#### (2) Between-group comparisons

(a) Parametric approach: For normally distributed data with homogeneous variances, one-way analysis of variance (ANOVA) is performed. If the omnibus test is significant (*p* < 0.05), *post hoc* pairwise comparisons are conducted using Tukey's HSD to control the family-wise error rate (FWER).

(b) Non-parametric approach: For non-normal or heteroscedastic data, the Kruskal–Wallis test is applied, followed by Dunn's test with Bonferroni-adjusted *p*-values (α = 0.017).

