#### (4) Sensitivity analysis

(a) Bonferroni correction: Directly applied to pairwise *t*-tests (adjusted α = 0.017).

(b) Multiple imputation: Missing values are imputed via chained equations (MICE algorithm) with 20 imputed datasets, incorporating baseline covariates and post-dropout outcomes (e.g., adverse events), which will validate results under missing-at-random assumptions. We add psychological status (baseline Hospital Anxiety and Depression Scale [HADS] scores), pain threshold (quantitative sensory testing [QST] for pressure pain tolerance at the trapezius muscle), and sociodemographic factors (age, sex, and education level) as the baseline covariates mentioned here to adjust for reliability of the subjective outcome measures.

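### The elimination criteria do not separate stopping treatment from removal from the analysis, and the main tests have no step for participants who meet them, so on the natural reading the primary comparison runs on a selected subset

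*Protocol article*

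**What the plan says.** The section "Discontinuation or elimination criteria" gives one list of six grounds. Two are behaviours after randomisation: item (5), "Participants with poor compliance did not adhere well to the study process", and item (6), "The participants received treatment outside the intervention". The other four are mistaken inclusion, a serious adverse event together with inconsistent participation, serious complications needing emergency care, and personal reasons. No item is assigned to discontinuation as opposed to elimination. The section does not say whether outcomes are still collected from these participants or whether they are analysed. Item (6) carries no time limit.

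For the main comparison, section (2) Between-group comparisons states: "For normally distributed data with homogeneous variances, one-way analysis of variance (ANOVA) is performed". Other data go to Kruskal–Wallis. Neither route has a step for missing or eliminated participants. Imputation appears only in section (4) Sensitivity analysis: "Missing values are imputed via chained equations (MICE algorithm) with 20 imputed datasets", a step "which will validate results under missing-at-random assumptions".

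On participant blinding the article contradicts itself. Blinding method says: "The participants will not be blinded due to the completely different therapies used in the three groups". Randomization and allocation concealment says: "Participants and outcome assessors are blinded to group assignments". Evaluators and statisticians are described as blinded in both sections.

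**The concern.** Adherence and use of other care arise after randomisation and can depend on both the arm and the response. A participant who knows the arm and is not improving is a plausible candidate to miss sessions or seek treatment elsewhere. If such participants are eliminated and the ANOVA or Kruskal–Wallis test runs on the rest, the groups compared are no longer those formed by randomisation. The result can then favour whichever arm loses more of its poor responders. The primary scales rest largely on symptoms, and the Limitations section itself concedes reporting bias from unblinded participants.

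The planned imputation does not settle this. It sits outside the main analysis, and it relies on missingness at random, which is doubtful when the reason for removal is non-adherence or seeking other care. The extension described under Limitations covers only those who complete the current trial, so eliminated participants would not return there.

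**Working it through.** **Is the subset stated or inferred?** Three statements have to be read together.

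1. The criteria list permits elimination for events after randomisation.
2. The between-group section analyses the data with no step that restores anyone.
3. Imputation, the only device that would restore them, is labelled a sensitivity analysis.

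A main comparison on a selected subset is the natural reading of the three. No sentence states it as a rule.

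**Inputs.** From Sample size estimation: SD σ = 8.2, δ = 5 points on CVS-FAS, 33 randomised per arm. The article gives no elimination rates by arm and no outcomes for those eliminated, so there is no figure of its own to reproduce on this point. The rates and gaps below are assumptions chosen to show a range.

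**Partial selection.** Suppose a share e of an arm is eliminated and their mean is g points worse than that of those retained. The full-arm mean is then the retained mean plus e·g, so elimination makes the arm look e·g points better. With the same g in two arms, the bias is g·(e₁ − e₂). The last column is the actual level of a single pairwise normal test at nominal two-sided 5%, with standard error 8.2·√(1/[33(1−e₁)] + 1/[33(1−e₂)]).

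| Eliminated, arm 1 v arm 2 | g | Bias (points) | Actual level |
|---|---|---|---|
| 10% v 10% | 4 or 8.2 | 0 | 5% |
| 15% v 5% | 4 | 4 × 0.10 = 0.40 | 5.4% |
| 15% v 5% | 8.2 | 8.2 × 0.10 = 0.82 | 6.7% |
| 20% v 0% | 4 | 4 × 0.20 = 0.80 | 6.6% |
| 20% v 0% | 8.2 | 8.2 × 0.20 = 1.64 | 11.9% |

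For 15% v 5% the standard error is 8.2·√(1/28.05 + 1/31.35) = 2.13.

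**Ceiling.** Suppose exactly the worst-responding fraction q of one arm is lost, nobody is lost elsewhere, and outcomes are normal. The shift in that arm's mean is σ·φ(z₁₋q)/(1 − q):

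- q = 5%: 8.2 × 0.1031/0.95 = 0.89 points, 18% of δ
- q = 10%: 8.2 × 0.1755/0.90 = 1.60 points, 32% of δ
- q = 15%: 8.2 × 0.2332/0.85 = 2.25 points, 45% of δ

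Nothing in the article selects perfectly on outcome, so these are upper limits for one-arm losses of that size and should not be read as expected values.

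**The case against.** The strongest reply is that the article never says the data of these participants leave the primary analysis. The heading offers discontinuation or elimination without assigning items, no analysis set is named, and analysis sets are commonly left to a full analysis plan, which is not shown here. That stands as far as it goes: the absence of a named set is not the point. What remains is that the article itself lists adherence and outside treatment as grounds for elimination and itself places imputation in the sensitivity tier. An all-randomised primary set defined elsewhere would still have to be reconciled with this list.

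A reader might infer several stronger points that the text does not support:

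- **Outcomes are deliberately not collected or are discarded.** No sentence says this. The imputation is to use outcomes observed after dropout, with adverse events as the example, so some later data collection is foreseen. It is not said to include the primary scales.
- **Safety failures are removed from the efficacy result.** Item (2) also requires inconsistent participation, and Safety evaluation leaves withdrawal after a serious event to the Ethics Committee.
- **Eliminations come on top of the 10% dropout allowance.** The sample size section does not say whether they are counted in it.
- **The trial is simply open-label.** Assessors and statisticians are blinded, every arm receives active acupuncture, and identical pre-treatment education is planned to equalise expectations. The two statements on participant blinding conflict.

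**Conclusion.** The point holds as an unresolved rule that, followed as written, can yield a selected primary comparison. It should be corrected, but it does not show that the result will be biased, or in which direction. On assumed figures the shift runs from 0 (equal losses equally related to response), through 0.40 to 0.82 points (15% v 5% eliminated, mean 4 to 8.2 points worse) and up to 1.64 points (20% v 0%). The ceilings are 0.9, 1.6 or 2.2 points for perfect selection of the worst 5%, 10% or 15% in one arm only. The yardstick is δ = 5. These figures rest on σ = 8.2 and on elimination patterns that the article does not give; the ceilings also assume normality. The mechanism is more plausible if participants know their arm, as Blinding method and Limitations say.

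**What to change.** Without changing any clinical stopping rule:

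- State that meeting a listed criterion after randomisation does not remove a participant from outcome collection or from the primary analysis.
- Continue the scheduled week 6, 12 and 24 assessments wherever the participant consents.
- Make the primary analysis one of all randomised participants in their allocated arm. Use either the 20-dataset imputation already planned, with arm, baseline score and earlier scores in the model, or a mixed model.
- Keep any compliance-based set as supportive only.
- Limit any exclusion for mistaken inclusion to facts that existed before randomisation, judged blind to arm, and report the number. This is the only exception to the all-randomised rule.
- Reconcile the two statements on participant blinding.

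The cost is protocol wording and some effort to keep contact for visits already in the schedule. The planned 33 per arm and 99 in total do not change. The small downside is that non-adherence may dilute the estimated difference.
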